## Visit 5: CONTRAINDICATIONS FOR INTERVENTION

*To be completed by study staff*

**Have you had any of the following symptoms?\***

**If YES, describe here:**

|                                                                      |                                                             |  |
|----------------------------------------------------------------------|-------------------------------------------------------------|--|
| Radiating pain
(burning,
numbness, or
tingling in the legs) |  Yes
 No |  |
| Muscle weakness
in the legs                                       |  Yes
 No |  |
| Episodes of
incontinence of
bowel or bladder                   |  Yes
 No |  |

\*If YES, describe in right column, refer to clinician for Health Status Reassessment Physical Exam, and complete Adverse Event Log (forms located in Appendix).

**Investigator Signature:** \_\_\_\_\_

**Date:** \_\_\_\_\_

DAY-MONTH-YEAR

Participant ID # \_\_\_\_\_

Visit Date \_\_\_\_/\_\_\_\_/\_\_\_\_

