### 7.1 Specification of Safety Parameters

At visits 2-9 the study staff will use the Health Status Reassessment CRF to ask the study participants if they have had any change in general health since the last visit. If fever or unexplained weight loss is reported, suggesting systemic infection / disease may be causing their low back pain, the clinician will do a basic physical exam and specifically assess for the possibility they have other systemic illness. They will be advised to seek medical care and research participation may be delayed, temporarily discontinued, or permanently suspended at the discretion of the examining clinician and in consultation with the Medical Directors if needed.

Before each treatment the study staff will use the Contraindications for Intervention CRF to inquire about change in back related signs indicative of increased severity of symptoms. Specifically if they have any increases in 1) radiating pain (i.e., burning, numbness, tingling sensations into the legs), 2) have noticed any muscle weakness in the legs, and 3) have any episodes of incontinence of bowel or bladder. If the study participant reports yes on any of these items the clinician will do a basic physical exam and assess neurological function by checking

myotomes, dermatomes, and reflexes to determine whether the study participant now presents with hard neurological signs (e.g., loss of motor function, significant changes in reflexes), or symptoms of other systemic disease. If the participant does present with hard neurological signs or serious systemic disease, they will be encouraged to seek consultation with their personal physician, and they will be excluded from further participation from the study.

Before each experimental measurement lab testing session (Visits 2, 8, and 9) the study staff will use the Contraindications for Lab Testing CRF to inquire specifically about symptoms of health issues contraindicated for the allocated experimental measurement lab test. Migraine headache will be assessed using The ID Migraine™ self-administered screener. If a possible contraindication is identified the PIs are consulted to determine safety before the lab testing begins.

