All negative changes in health status will be recorded as Adverse Events, logged, and reported per requirements of the Ohio University IRB and NIH-NCCIH. In the case of dismissal from the protocol for the above stated reasons, the Medical Safety Committee will meet to determine whether the AE was caused by the intervention (Definite, Probable, Possible, Unknown) and an adverse event report will be filed according to the specific requirements of the Ohio University IRB and NCCIH.

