**If YES, describe here:**

|                                                                      |                                                                 |  |
|----------------------------------------------------------------------|-----------------------------------------------------------------|--|
| Radiating pain
(burning,
numbness, or
tingling in the legs) |  Yes

 No |  |
| Muscle weakness
in the legs                                       |  Yes

 No |  |
| Episodes of
incontinence of
bowel or bladder                   |  Yes

 No |  |

\*If YES, describe in right column, refer to clinician for Health Status Reassessment Physical Exam, and complete Adverse Event Log (forms located in Appendix).

**Investigator Signature:** \_\_\_\_\_

**Date:** \_\_\_\_\_

DAY-MONTH-YEAR

Participant ID # \_\_\_\_\_

Visit Date \_\_\_\_/\_\_\_\_/\_\_\_\_

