## Visit 5: CHANGE IN MEDICATION USE

*To be completed by study coordinator*

Have you had any changes in medication use NOT related to your back pain in the past 7 days?

☐ No ☐ Yes (If YES, record below.)

| Medication | Indication* | Dose & Frequency | Start Date | Stop Date | Ongoing                  |
|------------|-------------|------------------|------------|-----------|--------------------------|
| 1.         |             |                  |            |           |  |
| 2.         |             |                  |            |           |  |
| 3.         |             |                  |            |           |  |
| 4.         |             |                  |            |           |  |
| 5.         |             |                  |            |           |  |

\*If Indication is related to a negative change in health status, alert study coordinator, complete Health Status Reassessment and enter in Adverse Event Log.

Notes:

Investigator Signature: \_\_\_\_\_

Date: \_\_\_\_\_

DAY-MONTH-YEAR

Participant ID # \_\_\_\_\_

Visit Date \_\_\_\_/\_\_\_\_/\_\_\_\_

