## Visit 5: HEALTH STATUS REASSESSMENT

*To be completed by study staff*

Since your last visit, have you had any change in your health?

☐ No ☐ Yes (If YES, record below, alert study coordinator, and complete Adverse Event log.)

|                                                                                                                                            |                                                                  |
|--------------------------------------------------------------------------------------------------------------------------------------------|------------------------------------------------------------------|
| Change & Symptoms                                                                                                               |                                                                  |
| Describe:

Start Date:
Stop Date:
Missed work or school? _____ days | Treatment:

Outcome: |
| Change & Symptoms                                                                                                               |                                                                  |
| Describe:

Start Date:
Stop Date:
Missed work or school? _____ days | Treatment:

Outcome: |
| Change & Symptoms                                                                                                               |                                                                  |
| Describe:

Start Date:
Stop Date:
Missed work or school? _____ days | Treatment:

Outcome: |

**Investigator Signature:** \_\_\_\_\_

**Date:** \_\_\_\_\_

DAY-MONTH-YEAR

Participant ID # \_\_\_\_\_

Visit Date \_\_\_\_/\_\_\_\_/\_\_\_\_

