## PHYSICAL EXAM - HEALTH STATUS REASSESSMENT

*To be completed by clinician if indicated in Health Status Reassessment*

This participant has self-reported a change in his or her health status and needs to be reassessed for adverse events and ability to participate in the study. Refer to HEALTH STATUS REASSESSMENT form for details and complete the form below based on findings.

| Category                                               | Normal or Abnormal                                                                                            | If abnormal, describe below |
|--------------------------------------------------------|---------------------------------------------------------------------------------------------------------------|-----------------------------|
| General Appearance                                     |  Normal
 Abnormal
 Not Examined |                             |
| Musculoskeletal                                        |  Normal
 Abnormal
 Not Examined |                             |
| Extremities/
Skin                                   |  Normal
 Abnormal
 Not Examined |                             |
| Neurological
(dermatomes,
myotomes,
reflexes) |  Normal
 Abnormal
 Not Examined |                             |
| Other, specify:
_____                               |  Normal
 Abnormal
 Not Examined |                             |

I certify this patient is:

- ☐ Able to continue study
  - ☐ Temporarily unable to continue in the study at this time due to a self-limited medical condition
    - ☐ Reassess health status in \_\_\_\_\_ days / weeks. (complete Protocol Deviation Form and Adverse Event Form)
  - ☐ Unable to continue in the study due to a serious change in medical status (complete Adverse Event Form, Protocol Deviation Form and Study Completion Form)
- ☐ I have recommended the participant seek medical care from his or her personal physician.

Investigator Signature: \_\_\_\_\_

Date: \_\_\_\_\_

DAY-MONTH-YEAR

Participant ID # \_\_\_\_\_

Visit Date \_\_\_\_/\_\_\_\_/\_\_\_\_

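### The radiating-pain row of the Visit 2–7 contraindications form sends any leg symptom to the Adverse Event Log, although section 7.1 uses that form to ask about increases

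*Supplement*

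**What the plan says.** Protocol section 7.1 names the form and states its purpose. Before each treatment, staff will "use the Contraindications for Intervention CRF to inquire about change in back related signs indicative of increased severity of symptoms". The first item is worded as a change: "Specifically if they have any increases in 1) radiating pain (i.e., burning, numbness, tingling sensations into the legs". The other two items, leg weakness and incontinence, are worded as any occurrence. A Yes to any item leads to a basic physical and neurological exam by the clinician. The recording rule follows later in the section: "All negative changes in health status will be recorded as Adverse Events".

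The form itself (CRF version 5.0, Contraindications for Intervention, identical at Visits 2 to 7) asks "Have you had any of the following symptoms" and offers Yes or No for radiating pain, leg weakness and incontinence. It gives no look-back period and does not mention increase, onset or baseline. Its footnote applies to every Yes: staff describe the symptom, then "refer to clinician for Health Status Reassessment Physical Exam, and complete Adverse Event Log".

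Other forms completed at the same visits are tied to change. Health Status Reassessment asks "Since your last visit, have you had any change in your health". Change in Medication Use carries the note "If Indication is related to a negative change in health status, alert study coordinator, complete Health Status Reassessment and enter in Adverse Event Log".

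**The concern.** For radiating pain, the protocol asks whether it has increased and the form asks whether it is present. A participant who enters with leg symptoms that never change would answer No to the protocol's question and Yes to the form's. On the form, that Yes goes straight to the Adverse Event Log.

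The log feeds the adverse event summary that section 7.2 sends to the independent monitors twice a year. Stable symptoms already documented at screening would appear there beside real events. Radiating leg symptoms are also among the signs that section 7.1 watches for worsening, so unchanged ones make a true increase somewhat harder to see in the counts.

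**Working it through.** No figure in the plan needs reproducing. The check sets the texts side by side and follows one participant through them.

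1. **Trigger.** Section 7.1, radiating pain: an increase. Form: any radiating symptom. Section 7.1, leg weakness and incontinence: any occurrence, which is what the form asks. The mismatch is therefore confined to the radiating-pain row.

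2. **Consequence of a Yes.** Section 7.1 attaches the clinician's exam to a Yes and deals with adverse event recording in a separate sentence about negative changes. The form's footnote joins exam and log entry in one instruction, so the entry does not wait for the exam result.

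3. **What belongs in the log.** Section 7.3 defines an adverse event as something untoward that arises while the person is taking part. The Adverse Events log asks about events during this study. The exam form to which the participant is referred opens with "This participant has self-reported a change in his or her health status" and describes the visit as a reassessment for adverse events. It calls for an Adverse Event Form under its two unable-to-continue outcomes, temporary and permanent, and says nothing about one under able to continue. All three fit a rule based on change or new occurrence; the footnote does not.

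4. **Can the case arise?** Section 4.1 requires three of four prediction-rule findings, and only one of them concerns leg symptoms. A participant can fail that one and still qualify. It covers only symptoms below the knee, so radiation into the thigh fails none of the four. Section 4.2 does not exclude leg radiation. Physical Exam Form 2 at Visit 1 records it by side and by whether it passes the knee.

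5. **Trace.** Take a participant with thigh tingling recorded at Visit 1 and unchanged since. At Visit 2, before the first treatment, section 7.1's question gets No: no increase and no negative change to record. The form's question gets Yes: exam and log entry. The same can recur at each later treatment visit. Forms carrying the row: 7 − 2 + 1 = 6.

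6. **Size.** Let *p* be the share of the 162 planned back-pain participants with leg symptoms at entry. The number with an unchanged baseline symptom logged is at most 162 × *p*. Each 10 percentage points in *p* adds at most 162 × 0.10 = 16.2, about 16 people. The documents give no value for *p*, so the possible range is 0 to 162, which says little. The ceiling assumes that everyone concerned answers Yes, stays unchanged and is logged.

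7. **Room for a forward correction.** The appendix on the supplemental study reports 18 + 31 = 49 of 27 + 33 = 60 Experiment 2 participants already tested (49/60 = 82%). The funder's June 2016 message describes the back-pain part as almost complete.

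**The case against.** The best reply is that the form is a deliberately broad screen within a pathway that sorts things out later. Asking about any radiating symptom before a thrust manipulation is cautious. The question follows directly after the Health Status Reassessment, which has just asked about change since the last visit. Section 7.1 tells trained staff what the form is for, and section 7.3 and the log heading tell them what counts. The log has start-date and attribution columns, and the Medical Director reviews events where applicable. Much of this stands: staff are not without guidance, and some unchanged symptoms would probably be left out or be recognisable in the log. What does not stand is that it removes the conflict. Even if a since-last-visit period is understood, a persistent symptom is still a Yes, and the footnote orders the log entry without asking for a comparison with baseline. An entry marked unrelated is still an entry.

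A reader might also infer that the form breaches the recording rule in section 7.1. It does not: "All negative changes in health status will be recorded as Adverse Events" says that all such changes are recorded, not that only they are, and recording more than that does not break it. The conflict is with the sentence about increases.

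**Conclusion.** The point holds as a minor inconsistency between form and protocol. Followed as written, the radiating-pain row can place an unchanged baseline leg symptom in the Adverse Event Log, including before treatment has begun, whereas section 7.1 intends the row to pick up increases.

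The size cannot be stated. The effect is limited to extra entries in descriptive adverse event counts and in the twice-yearly summary. A reader might infer that safety is weakened, that the arms are compared unfairly, or that the trial could be stopped wrongly. The documents support none of these. The form asks more than section 7.1 requires, so no check is lost. The same form is used in all three arms, and no difference between them is shown. Section 9 plans no comparison of adverse events between arms. The stopping provision in section 9.3 turns on excessive serious events, which an unchanged leg symptom would not be.

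The conclusion rests on the version 5.0 forms of 21 April 2016, the latest shown. The investigator's June 2016 message says that the e-CRFs were modified for protocol version 6.0. Nothing suggests that this row was among the changes, but it cannot be excluded.

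**What to change.** First confirm that the e-CRFs in use with version 6.0 still carry the row as shown. If they do, restrict the log instruction for the radiating-pain row to new or increased radiating pain since the last visit (at Visit 2, since screening). Keep the clinician's exam for any radiating symptom, and leave the leg-weakness and incontinence rows and section 7.1 as they are.

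With recruitment of back-pain participants nearly finished, the more useful step is retrospective. For entries already made, compare the Visit 1 leg-radiation record with the form's description column and the event start date. Flag radiating symptoms unchanged from baseline and summarise them separately from adverse events.

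The cost is one row on six forms and a flag built from data already collected. No new data and no protocol change are needed.

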## Visit 5: NUMERIC PAIN RATING SCALE (NPR)

To be completed by assessment team member

[figure not shown]

### Instructions:

Sometimes it is helpful to think about the Numeric Rating Scale in the following manner:

- 0 = No Pain
- 1-3 = Mild Pain (nagging, annoying, interfering little with your activities of daily living)
- 4-6 = Moderate Pain (interferes significantly with your activities of daily living)
- 7-10 = Severe Pain (disabling; unable to perform your activities of daily living)

Please indicate:

- What number would you give your pain right now?
- What number would describe your pain since your last visit?

**Since your last visit** how would you answer the next 3 questions:

What number on a 0 to 10 scale would you give your pain when it is the worst that it gets?

- What number on a 0 to 10 scale would you give your pain and when it is the best that it gets?
- At what number is the pain at an acceptable level for you?

Investigator Signature: \_\_\_\_\_

Date: \_\_\_\_\_

DAY-MONTH-YEAR

## Visit 5 (Intervention 4): INTERVENTION ADMINISTRATION LOG

To be completed by clinician

[figure not shown] **All fields must be completed**

|                                     |                                                                           |                      | L1                                        | L2                                        | L3                                        | L4                                        | L5                                        |                |
|-------------------------------------|---------------------------------------------------------------------------|----------------------|-------------------------------------------|-------------------------------------------|-------------------------------------------|-------------------------------------------|-------------------------------------------|----------------|
| Pre-Intervention Assessment  | Symmetry of Active Side Bending

SBL cm

SBR cm | Transverse Process   | FRS-L
FRS-R                            | FRS-L
FRS-R                            | FRS-L
FRS-R                            | FRS-L
FRS-R                            | FRS-L
FRS-R                            |                |
|                                     |                                                                           |                      | ERS-L
ERS-R                            | ERS-L
ERS-R                            | ERS-L
ERS-R                            | ERS-L
ERS-R                            | ERS-L
ERS-R                            |                |
|                                     |                                                                           |                      | NORM                                      | NORM                                      | NORM                                      | NORM                                      | NORM                                      |                |
|                                     |                                                                           | P-A Translation      | Hypermobile
Hypomobile
Normal
NA | Hypermobile
Hypomobile
Normal
NA | Hypermobile
Hypomobile
Normal
NA | Hypermobile
Hypomobile
Normal
NA | Hypermobile
Hypomobile
Normal
NA |                |
| Intervention                 |                                                                           | # of Thrusts Applied | 1 2 3 4
NA                             | 1 2 3 4
NA                             | 1 2 3 4
NA                             | 1 2 3 4
NA                             | 1 2 3 4
NA                             |                |
|                                     |                                                                           | Audible Response     | Yes No
NA                              | Yes No
NA                              | Yes No
NA                              | Yes No
NA                              | Yes No
NA                              |                |
| Post-Intervention Assessment | SBL cm

SBR cm                                        | P-A Translation      | Hypermobile
Hypomobile
Normal
NA | Hypermobile
Hypomobile
Normal
NA | Hypermobile
Hypomobile
Normal
NA | Hypermobile
Hypomobile
Normal
NA | Hypermobile
Hypomobile
Normal
NA |                |
|                                     |                                                                           |                      | Transverse Process                        | FRS-L
FRS-R                            | FRS-L
FRS-R                            | FRS-L
FRS-R                            | FRS-L
FRS-R                            | FRS-L
FRS-R |
|                                     |                                                                           |                      |                                           | ERS-L
ERS-R                            | ERS-L
ERS-R                            | ERS-L
ERS-R                            | ERS-L
ERS-R                            | ERS-L
ERS-R |
|                                     |                                                                           | NORM                 |                                           | NORM                                      | NORM                                      | NORM                                      | NORM                                      |                |

Notes:

Investigator Signature: \_\_\_\_\_

Date: \_\_\_\_\_

DAY-MONTH-YEAR

Participant ID # \_\_\_\_\_

Visit Date \_\_\_\_/\_\_\_\_/\_\_\_\_

---

## VISIT 5: CHECKLIST

---

*To be completed by study coordinator*

7. Did the participant attend this visit? ☐ Yes (if yes, continue) ☐ No  
8. Please check all assessments completed at this visit:

